### Randomisation

A third-party, Internet-based, data collection and randomisation system will be used to confirm participant eligibility and ensure allocation concealment; that is, participant allocations are concealed within the system until the patient is randomised. Only participants who meet the eligibility criteria can be randomised. In instances where computer or Internet access is not reliable, participants will be randomised using sequentially numbered, opaque, sealed envelopes. Dedicated PIP study personnel will be responsible for randomising participants at each site. Participants will be randomised in a 1:1 ratio using block randomisation of two different sizes between 5–15 repeating in random order, stratified by recruiting clinic and by fresh or frozen-thaw embryo transfer (the latter in PIP-IVF only).

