### Statistics

#### Sample size

##### PIP-IVF

Based on the results of a Cochrane review on endometrial injury for IVF, a difference between arms of 16 % may be expected (pooled live birth rates of 33 % and 17 % [43]). At 90 % power and a significance level of 5 % in a two-sided test, at least 188 women are required in each arm (376 in total). In order to power for detection of any subgroup differences (for example, whether endometrial injury increases live birth rate in women undergoing frozen-thaw transfers) and assuming an equal recruitment of fresh and frozen transfer, the required sample was doubled, raising the total number required to 752.

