##### PIP-UE

Current rates of pregnancy in women with unexplained infertility undergoing expectant management are approximately 3 % per cycle [44]. An expected increase in pregnancy rates to 9 % in the biopsy arm might be expected based on previous studies. With 3 months of expectant management, this equates to an expected cumulative difference of 25 % vs 9 % in the biopsy and sham arms respectively. With an adjustment for live birth rates, which are generally 19 % lower than pregnancy rates [45], the expected difference becomes 20 % vs. 7 %. At 90 % power and a significance level of 5 % in a two-sided test, 158 women are required in each arm (316 in total).

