##### PIP-PCOS

PIP-PCOS sample size is based on the PCOS I trial, where a live birth rate per visit in the clomiphene arm was 5 % for the first 3 months [46]. An increase to 12 % per cycle as per previous studies might be expected. At 90 % power and a significance level of 5 % in a two-sided test, 126 women are required in each arm (252 in total).

Applying a 10 % contingency in each study to account for 1) women allocated to the biopsy group who fail to have a biopsy due to difficulty passing the pipelle, and 2) for participant attrition, the following numbers of participants are required in each study: PIP-IVF = 840, PIP-UE = 350, PIP-PCOS = 280. In the context of growing uncertainty regarding the beneficial effects of endometrial scratching, a power of 90 % was selected to reduce the probability of a type 2 error.

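### PIP-IVF sample size: 188 women per arm does not follow from 33% v 17% at 90% power; it gives about 95% power, so the stated power, the rates or the size is misstated (in the conservative direction)

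*Protocol article*

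**What the plan says.** In the protocol article, under Sample size, PIP-IVF, the planning assumption comes from a systematic review: "a difference between arms of 16 % may be expected", from "pooled live birth rates of 33 % and 17" per cent. The size follows directly, for 90% power and a two-sided 5% level: "at least 188 women are required in each arm (376 in total"). The 376 is then doubled to 752 so that effects in the fresh and frozen transfer groups can be studied.

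The closing paragraph under PIP-PCOS applies a 10% contingency to all three trials and lists the final targets, 840 for PIP-IVF. It also says, for the trials together, that "a power of 90 % was selected to reduce the probability of a type 2 error". Under Randomisation, allocation is equal: "Participants will be randomised in a 1:1 ratio".

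**The concern.** The article gives both rates, the power, the level, the sidedness, the allocation and the result. A reader can therefore repeat the calculation, and it does not come out. This is not a detail left to a fuller document, because inputs and output stand in the same paragraph and disagree.

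The figure matters because 188 is the root of the chain to 840, and because 90% is presented as a deliberate choice. A reader who takes the paragraph at face value is misinformed about the power, the effect assumed, or the number that effect requires.

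**Working it through.** **Inputs** (Sample size, PIP-IVF; Randomisation): p1 = 0.33, p2 = 0.17, difference d = 0.16, mean rate 0.25, two-sided 5% (z = 1.960), 90% power (z = 1.2816), 1:1 allocation.

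**1. Attempt to reproduce 188.** The pooled-variance formula per arm is

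n = [z(alpha) × √(2 × 0.25 × 0.75) + z(power) × √(0.33 × 0.67 + 0.17 × 0.83)]² / d²

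- First term: 1.960 × √0.375 = 1.960 × 0.6124 = 1.2002
- Second term: 1.2816 × √0.3622 = 1.2816 × 0.6018 = 0.7713
- n = (1.9715)² / 0.0256 = 151.8, so **152 per arm**

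With continuity correction: n' = (n/4) × [1 + √(1 + 4/(n × d))]² = (151.8/4) × [1 + √(1 + 4/24.29)]² = 164.1, so **165 per arm**.

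**2. Other standard methods, same inputs.**

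| Method | Per arm at 90% power |
|---|---|
| Pooled variance | 152 |
| Unpooled variance | 149 |
| Arcsine | 151 |
| Continuity-corrected | 165 |
| Fisher exact | between 160 (89.5%) and 164 (90.4%) |
| Stated | 188 |

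**3. Power that 188 delivers.** z = (√188 × 0.16 − 1.2002) / 0.6018 = (2.1938 − 1.2002) / 0.6018 = 1.651, so power is **95.1%**. With continuity correction it is 93.7%, and by Fisher's exact test 93.9%. Conversely, putting 95% power (z = 1.6449) into the uncorrected formula gives 187.4, which rounds up to exactly 188.

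**4. Could rounding of the rates explain it?** If 33% and 17% are rounded and the true difference still rounds to 16%, the largest result at 90% power is 164, or 176 corrected. If that condition on the difference is dropped and both rates sit at the extreme edge (32.5% v 17.5%), the result is 174, or 187 corrected. That is close to 188 but short of it, and it needs a difference of 15 points instead of the stated 16.

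**5. The later steps.** 188 × 2 = 376; 376 × 2 = 752; 752 / 0.9 = 835.6, stated as 840. These are consistent with 188.

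**6. The same steps from the stated inputs.** 152 × 4 = 608 and 608 / 0.9 = 675.6, so 676. Corrected: 165 × 4 = 660 and 660 / 0.9 = 733.3, so 734. The target of 840 exceeds these by 164 and 106 women.

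**The case against.** The strongest reply is that nothing is lost. Power for the stated effect exceeds the 90% promised, the analysis is unaffected, and a reader who knows the rates, level and size can see that power is adequate. That stands, and it limits the weight of the point. It does not remove the disagreement between the printed inputs and the printed result.

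The rates come from a review that is not at hand and are given as whole percentages, so the size of the excess is less certain than the two figures of 106 and 164 suggest. This also stands. Rounding narrows the gap but does not close it.

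A reader might also infer more than the article supports:

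- **That 376, 752 and 840 are wrong.** They follow correctly from 188. If only the power label is wrong, all of them stand.
- **That the three trials were sized by different rules.** The continuity-corrected formula gives 158.1 for PIP-UE's 20% v 7%, close to the stated 158, but so does the uncorrected 143.1 × 1.1 = 157.4, rounded up. For PIP-PCOS, cumulating 5% and 12% over three cycles (14.3% v 31.9%) gives 119 uncorrected or 130 corrected, and neither is the stated 126. Neither a common rule nor different rules can be shown.
- **That the 10% contingency was counted twice.** Cutting both rates by 10% (29.7% v 15.3%) gives a corrected 188.3, but nothing in the article says that 188 contains an allowance for loss. The contingency appears once, after the doubling.

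**Conclusion.** The point holds in a narrow form. For 33% v 17%, two-sided 5% and equal allocation, 90% power needs 152 women per arm, or about 165 with continuity correction. At 188 per arm the power is about 95% (94% corrected). The stated power, rates and size cannot all be right.

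Which one is wrong cannot be settled from the article. A calculation at 95% power labelled as 90% fits exactly, but that is inference. Rates of 33% v 18% with continuity correction give 188.4, which is nearly as close.

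The error is conservative: PIP-IVF is larger than its stated inputs require and loses no power for the stated effect. The 95% refers to the calculation at 188 per arm, before the doubling. The conclusion takes the printed rates at face value and assumes a conventional test of two proportions.

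**What to change.** Keep 188, 376, 752 and 840. Check the original calculation, then do one of the following:

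- Under Sample size, PIP-IVF, state that with live birth rates of 33% and 17% and a two-sided 5% level, 188 women per arm give about 95% power (no continuity correction) or about 94% (with it), and name the formula used.
- If other rates produced 188 at 90% power, state those rates and the formula.

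In the first case, also qualify the statement at the end of the PIP-PCOS section that 90% power was selected, so that it no longer describes PIP-IVF as sized at 90%.

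The cost is one corrected sentence and one short qualification. Recruitment, randomisation and analysis are unchanged.

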## Methods/design

The PIP studies are pragmatic, parallel, multi-centre, superiority RCTs.

The pragmatic nature of the studies is a result of the broad inclusion criteria, time frame in which the intervention is administered and lack of restriction to specific stimulation or ovulation induction protocols. This rationale is based on the existing evidence in favour of endometrial scratching before IVF, in which a benefit has been shown across a range of time frames for performing the intervention and in different patient populations. Inclusion of a heterogeneous population in a large study provides an opportunity to detect treatment effects within different patient subgroups.

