### Statistical analysis

Demographic and baseline data will be compared between the two groups using the chi-squared test or *t*-test. Outcome data for the primary analyses will be treated in an intention-to-treat manner, such that all participants remain in the groups to which they were randomised. If no outcome data is available for the primary outcome of live birth, this will be imputed to assume that women with no outcome data did not have a live birth. Sensitivity analyses based on different assumptions may be used for secondary analyses. Per protocol analyses will be conducted as a secondary analysis.

For binary outcomes (for example, live birth), risk ratios will be calculated with associated 95 % confidence intervals and *p* values. ANOVA or logistic regression analysis will be used for the analysis of pre-specified subgroup effects. For continuous outcomes (such as pain), the mean difference will be calculated and the student’s *t*-test will be used.

Assessment of participant blinding will be performed using both James’ and Bang’s blinding indices [47, 48]. All statistical analysis will be performed using STATA or a similar statistical programme.

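### Doubling PIP-IVF to 752 powers the effect within fresh and within frozen transfers, not subgroup differences in general as the Sample size section says

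*Protocol article*

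**What the plan says.** The Sample size section for PIP-IVF starts from "pooled live birth rates of 33 % and 17" per cent and concludes: "At 90 % power and a significance level of 5 % in a two-sided test, at least 188 women are required in each arm (376 in total"). It then gives the reason for going further: "In order to power for detection of any subgroup differences". The example that follows asks whether injury raises live birth among women having frozen-thaw transfers. The step itself is: "assuming an equal recruitment of fresh and frozen transfer, the required sample was doubled, raising the total number required to 752". No size of difference between fresh and frozen is specified.

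Elsewhere in the protocol article:

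- Methods/design says that a large heterogeneous sample "provides an opportunity to detect treatment effects within different patient subgroups".
- Randomisation is 1:1 and "stratified by recruiting clinic and by fresh or frozen-thaw embryo transfer (the latter in PIP-IVF only"), with no quota for either transfer type.
- Statistical analysis takes the risk ratio as the measure for binary outcomes and adds: "ANOVA or logistic regression analysis will be used for the analysis of pre-specified subgroup effects". It does not say whether this means an interaction test.
- The first list under Subgroup analyses (headed PIP-UE, but made up of embryo-transfer items) has 11 factors, several with three or more levels. One is single or double transfer, and the PIP-IVF eligibility text limits double transfers to 20% of women.

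**The concern.** A subgroup difference, in the usual sense, is a difference between two treatment effects. Its variance is the sum of the variances of the two effects, so a sample that is adequate for each effect alone is not adequate for a contrast of similar size between them. Doubling the single-comparison sample supplies the two within-half comparisons and nothing more. The sentence also speaks of subgroup differences without limit, although the doubling is tailored to one two-level factor with an assumed equal split.

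This is the only reason given for doubling the trial. A reader who takes it at face value could treat a significant result in one transfer type and a non-significant result in the other as a difference the trial was sized to detect, or treat a non-significant interaction as good evidence that the effects are alike.

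**Working it through.** **Inputs from the protocol article.** Rates 33% and 17%; two-sided 5%; 90% power; 188 per arm; 752 in total, split equally between fresh and frozen (Sample size, PIP-IVF); 1:1 allocation (Randomisation); double transfers at most 20% (Eligibility, PIP-IVF). **Assumptions not in the document:** the effect in the second half, and a 17% control rate in both halves.

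**1. The plan's own figure.** With the pooled normal approximation,

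n per arm = [1.960·√(2·0.25·0.75) + z·√(0.33·0.67 + 0.17·0.83)]² / 0.16².

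For 90% power (z = 1.282) this is 151.8, so 152 (165 with continuity correction). For 95% power (z = 1.645) it is 187.4, so 188. The printed 188 is therefore not reproduced at 90%; it matches 95%. The doubling is arithmetically right: 2 × 376 = 752, or 188 per arm in each half.

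**2. Power within a subgroup for 33% v 17%.** Power = Φ[(0.16·√n − 1.960·√0.375) / √0.3622], with n = 752 × share / 2.

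| Share of women | n per arm | Power |
|---|---|---|
| 50% (equal halves) | 188 | 95% |
| 40% | 150 | 90% |
| 30% | 113 | 80% |
| 20% (double transfers at their cap) | 75 | 62% |

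**3. Power for the difference in effect, fresh v frozen.** There are four cells of 188. Power = Φ(D/SE − 1.960) and SE = √(V/188). D is the difference between the two effects. V sums over the four cells p(1−p) for the risk difference, 1/[p(1−p)] for the log odds ratio, and (1−p)/p for the log risk ratio.

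| Pattern | Scale | D | SE | Power |
|---|---|---|---|---|
| 33 v 17 and 17 v 17 | Risk difference | 0.160 | 0.0585 | 78% |
| | Logistic | 0.877 | 0.370 | 66% |
| | Risk ratio | 0.663 | 0.298 | 61% |
| 33 v 17 and 25 v 17 | Risk difference | 0.080 | 0.0606 | 26% |
| | Logistic | 0.390 | 0.358 | 19% |
| | Risk ratio | 0.278 | 0.280 | 17% |

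For the first pattern, simulation with 40,000 runs gave 66% (logistic) and 78% (risk difference).

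**4. Sensitivity.**

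- Second half null at 33 v 33: 69% (risk difference), 75% (logistic), 78% (risk ratio).
- Null rate in the second half varied from 10% to 33%: roughly 44% to 85% across the three scales.
- All 840 women analysed, 210 per cell, first pattern: 82%, 71% and 65% in the same order.
- Effect reversed in the second half (9 v 17): 99%, 98% and 97%.

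**5. Total for 90% interaction power, first pattern.** n per cell = V·(1.960 + 1.282)²/D². On the risk-difference scale V = 0.6444, giving 265 per cell and 1,060 in total. On the logistic scale V = 25.78, giving 352 per cell and 1,408 in total.

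**The case against.** The strongest defence is that the authors meant effects within subgroups. The passage opens with a difference between arms, its example concerns one transfer type only, and Methods/design also speaks of effects within subgroups. On that reading doubling works for fresh and frozen, with about 95% power against a stated 90%, and the equal split is openly an assumption. This stands and limits the point to the wording. It does not rescue the unlimited claim, because even within-subgroup power fails for a factor as unbalanced as double transfer.

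A reader might infer more than the document supports:

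- **That 66% is a ceiling for the interaction.** It is one scale and one scenario. The same pattern gives 78% on the risk-difference scale, which is what ANOVA on a binary outcome would use, and ANOVA is one of the two methods named. A full effect against none is also not the largest possible contrast: a reversed effect is well powered, and the Discussion allows that scratching could be detrimental.
- **That discordant results in the two halves would be mostly chance.** If both halves truly have the planned effect, exactly one is significant in 2 × 0.951 × 0.049, or about 9% of trials. The share rises only if the true effect is smaller than planned. Nothing in the protocol says discordant results would be reported as a powered difference.
- **That the main comparison is weakened.** At 376 per arm, power for 33% v 17% exceeds 99%.

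The full set of interaction models may fairly be left to an analysis plan. The power claim is made here, so it has to be right here.

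**Conclusion.** The concern holds as a misstated power property. The 752 women power the treatment effect within fresh and within frozen transfers if recruitment is about equal. They do not give 90% power for a full-versus-no-effect contrast between the two on any of the three scales at a 17% control rate, and power is low for a full-versus-half contrast. They also do not power the listed embryo-transfer subgroups in general. The interaction figures rest on 188 women per cell and on the assumed rates. They move with the scale and with the rate in the null half, so they should be quoted as ranges or tied to one chosen scale. The primary analysis is unaffected. Separately, the shortfall remains even though 188 per arm is more than the stated 90% requires.

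**What to change.** In the PIP-IVF sample size text:

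1. Replace the general claim about subgroup differences with a statement that 752 women power the comparison of arms within fresh and within frozen transfers, provided recruitment is equal. Add that power falls to about 80% in a half holding 30% of women.
2. Give the power of the treatment-by-transfer-type interaction with its assumptions (188 per arm per half, 17% control rate in both): 61–78% for 16 v 0 points and 17–26% for 16 v 8 points. Alternatively, give the single figure that matches the scale of the chosen test, for example 61% and 17% if the interaction is tested on the risk-ratio scale.
3. State that any claim that the effect differs between fresh and frozen rests on that interaction test.
4. Describe the remaining embryo-transfer subgroups as not powered.
5. While editing, reconcile 188 per arm with the stated 90% power.

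The cost is wording only, with no extra patients. The price is that the stated subgroup power becomes less favourable.

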##### PIP-UE

Current rates of pregnancy in women with unexplained infertility undergoing expectant management are approximately 3 % per cycle [44]. An expected increase in pregnancy rates to 9 % in the biopsy arm might be expected based on previous studies. With 3 months of expectant management, this equates to an expected cumulative difference of 25 % vs 9 % in the biopsy and sham arms respectively. With an adjustment for live birth rates, which are generally 19 % lower than pregnancy rates [45], the expected difference becomes 20 % vs. 7 %. At 90 % power and a significance level of 5 % in a two-sided test, 158 women are required in each arm (316 in total).

##### PIP-PCOS

PIP-PCOS sample size is based on the PCOS I trial, where a live birth rate per visit in the clomiphene arm was 5 % for the first 3 months [46]. An increase to 12 % per cycle as per previous studies might be expected. At 90 % power and a significance level of 5 % in a two-sided test, 126 women are required in each arm (252 in total).

Applying a 10 % contingency in each study to account for 1) women allocated to the biopsy group who fail to have a biopsy due to difficulty passing the pipelle, and 2) for participant attrition, the following numbers of participants are required in each study: PIP-IVF = 840, PIP-UE = 350, PIP-PCOS = 280. In the context of growing uncertainty regarding the beneficial effects of endometrial scratching, a power of 90 % was selected to reduce the probability of a type 2 error.

### Statistical analysis

Demographic and baseline data will be compared between the two groups using the chi-squared test or *t*-test. Outcome data for the primary analyses will be treated in an intention-to-treat manner, such that all participants remain in the groups to which they were randomised. If no outcome data is available for the primary outcome of live birth, this will be imputed to assume that women with no outcome data did not have a live birth. Sensitivity analyses based on different assumptions may be used for secondary analyses. Per protocol analyses will be conducted as a secondary analysis.

For binary outcomes (for example, live birth), risk ratios will be calculated with associated 95 % confidence intervals and *p* values. ANOVA or logistic regression analysis will be used for the analysis of pre-specified subgroup effects. For continuous outcomes (such as pain), the mean difference will be calculated and the student’s *t*-test will be used.

Assessment of participant blinding will be performed using both James’ and Bang’s blinding indices [47, 48]. All statistical analysis will be performed using STATA or a similar statistical programme.

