### Outcomes

The primary outcome is live birth rate per woman randomised, as defined previously [35].

Secondary outcomes include:ongoing pregnancy per woman randomised (defined as continuing pregnancy diagnosed by ultrasonographic visualisation of one or more gestational sacs on or after 12 weeks gestation)clinical pregnancy per women randomised (defined as a pregnancy diagnosed by ultrasonographic visualisation of one or more gestational sacs, including ectopic pregnancy)biochemical pregnancy (defined as βhcg > 25 mIU/ml) PIP-IVF onlymultiple pregnancies per women randomised and per clinical pregnancy (defined as ultrasonographic visualisation of two or more gestational sacs or heartbeats)ectopic pregnancy per women randomised and per clinical pregnancy (defined as a pregnancy in which implantation takes place outside the uterine cavity)miscarriage per women randomised and per clinical pregnancy (defined as the spontaneous loss of a clinical pregnancy before 20 completed weeks of gestational age)neonatal characteristics (for example, gender, gestation at birth, malformations)placenta characteristics (placenta previa: major, placenta previa: minor, placental abruption, placenta accreta: previous uterine surgery, placenta accreta: no previous uterine surgery)pain during the procedure (as measured by a 10 cm visual analogue scale (VAS))bleeding the day following the procedure.

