#### ᅟ

##### PIP-UE

Type of embryo transfer (fresh or frozen)Number of embryos transferred (single or double)Number of previous embryo transfer procedures not resulting in a clinical pregnancy (for example, 0–1, 2–4, ≥5)Number of embryos transferred previously not resulting in a clinical pregnancy (for example, 0–1, 2–4, ≥5)Timing of endometrial biopsy (for example, follicular phase: cycle prior to embryo transfer cycle, luteal phase: cycle prior to ET cycle, follicular phase: embryo transfer cycle)Major cause of infertility (for example, male factor, endometriosis, ovulatory factor, unexplained, tubal factor, other)History of endometriosis (endometriosis or no endometriosis)Type of IVF (IVF or ICSI)Type of stimulation protocol (for example, long agonist, ultralong agonist, short agonist, antagonist)Duration of infertility (for example, < 2 years, 2–5 years, >5 years)Stage of embryos at transfer (for example, day 5/6 or day 2/3)

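### Randomisation is stratified by clinic (and by fresh/frozen transfer in PIP-IVF), but the primary risk ratio names no stratification factor; as written the analysis is valid but mildly conservative

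*Protocol article*

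**What the plan says.** The Randomisation section of the protocol article states: "Participants will be randomised in a 1:1 ratio using block randomisation", "stratified by recruiting clinic and by fresh or frozen-thaw embryo transfer (the latter in PIP-IVF only". Clinic is therefore a stratum in all three trials. Transfer type is a stratum in PIP-IVF alone.

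Under Outcomes: "The primary outcome is live birth rate per woman randomised". Under Statistical analysis: "For binary outcomes (for example, live birth), risk ratios will be calculated with associated" 95% confidence intervals and p values. Continuous outcomes get a mean difference and Student's t-test. Modelling is mentioned once: "ANOVA or logistic regression analysis will be used for the analysis of pre-specified subgroup effects".

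Transfer type also appears as a subgroup factor for live birth ("Type of embryo transfer (fresh or frozen"). That list is printed under a PIP-UE heading, although its content concerns embryo transfer. No statement says whether the main comparison is adjusted or unadjusted.

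**The concern.** Stratified blocks balance the arms on the stratifying factors. If those factors predict live birth, the difference between arms varies less from trial to trial than under simple randomisation. A two-group variance formula does not take credit for this, so the interval is somewhat too wide and the test somewhat conservative.

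Prognostic strata are plausible here. The ethics approvals cover sites in New Zealand, Australia, Egypt, Brazil, Sweden and Belgium, and the Standard care section allows stimulation protocols to differ by centre. What is at stake is precision and a little power, not the validity of the conclusions.

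**Working it through.** **1. The plan's own figure.** Inputs from the PIP-IVF sample size section: "pooled live birth rates of 33 % and 17" per cent, and "At 90 % power and a significance level of 5 % in a two-sided test, at least 188 women are required" in each arm. The usual two-proportion formula is

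n = [z₀.₉₇₅·√(2p̄(1−p̄)) + z_power·√(p₁(1−p₁)+p₂(1−p₂))]² / (p₁−p₂)²

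With p₁ = 0.33, p₂ = 0.17 and p̄ = 0.25, the two roots are 0.612 and 0.602.
- 90% power: (1.960×0.612 + 1.282×0.602)² / 0.0256 gives 152 per arm (165 with continuity correction).
- 95% power: (1.960×0.612 + 1.645×0.602)² / 0.0256 gives 188 per arm.

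The stated 188 is therefore not reproduced at 90% power and matches 95%. That is a separate matter. It leaves more women than 90% power needs and does not bear on stratification.

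**2. Closed-form size of the effect.** The assumptions, which are not in the article, are a mean live birth rate of 25% and a between-stratum SD of 8 or 12 points.
- Share of variance explained by strata: R² = SD²/[p(1−p)] = 0.0064/0.1875 = 0.034, or 0.0144/0.1875 = 0.077.
- Standard error excess of the unadjusted analysis: 1/√(1−R²) − 1 = 1.8% or 4.1%.
- True two-sided type I error: 2[1−Φ(1.96/√(1−R²))] = 4.6% or 4.1%.
- Extra women an unadjusted analysis of 840 would need to match: 840·R²/(1−R²) = about 30 or 70.

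**3. Simulation for PIP-IVF.** There were 10,000 runs per scenario, comparing the unadjusted risk ratio and chi-squared test with the Mantel-Haenszel risk ratio and Cochran-Mantel-Haenszel (CMH) test. Assumptions: 10 equal clinics, exact balance within strata, and the between-clinic logit SD and the fresh/frozen logit difference both set to the value in the first column. Monte Carlo error on a 5% rate is √(0.05×0.95/10,000) = 0.2 points.

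| Spread | SE excess, unadjusted | Type I error, chi-squared / CMH | Power at about 752 women, 26.5% vs 17%, chi-squared / CMH |
|---|---|---|---|
| 0 | 0% | 4.8 / 4.7% | 88.6 / 88.6% |
| 0.3 | 0.7–0.9% | 4.5 / 4.8% | 89.1 / 89.4% |
| 0.5 | 2.0–2.2% | 4.4 / 4.9% | 89.8 / 90.5% |
| 0.8 | 4.9–5.4% | 3.6 / 4.6% | 90.2 / 92.0% |

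The last row is extreme: control live birth rates run from 3% to 48% across strata. Coverage of the unadjusted interval under the null was 95.4–96.6%. At the planned 33% vs 17%:
- with about 188 per arm (180 simulated), power was 94.5 vs 94.3%, 94.5 vs 94.7%, 95.1 vs 95.6% and 95.5 vs 96.5%, in the same order of spread;
- with about 752 women, it was above 99.9% for both methods.

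**4. PIP-UE and PIP-PCOS** (clinic strata only). Over the same spreads the standard error excess reached 2.3% and 3.8%, and the power loss was at most about 1 point.

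**5. Subgroup scale.** A logistic interaction is measured on the odds scale, while the main effect is a risk ratio. With control rates of 17% and 30% and a constant risk ratio of 1.42 (the review's live birth figure in the Background), the odds ratios are 1.55 and 1.73, a ratio of 1.11. With a risk ratio of 1.94 (33/17) they are 2.40 and 3.25, a ratio of 1.35, but that implies a treated live birth rate of 1.94 × 30% = 58%.

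**The case against.** The strongest reply is that the article never calls the risk ratio crude. A Mantel-Haenszel or modified Poisson risk ratio fits the same sentence, and the covariates of a primary model are often left to the analysis plan, which is not shown. This stands in part: a reader might infer that the trials have committed to ignoring the strata, and the text does not say so. But beside a plain t-test, and with regression named only for subgroups, an analyst following the section as written would run an unstratified comparison.

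A second reply is that an unadjusted analysis is simple, valid and avoids sparse clinics. That stands. A reader might infer that the confidence intervals are wrong. They are not: type I error stays at or below 5% and coverage at or above 95%.

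A third is that the spreads are assumed and that the article expects standard care to differ only slightly between centres. That also stands, and it is why a range is given.

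Finally, a reader might infer that the subgroup plan will manufacture interactions, or that ANOVA will be run on live birth. The text does not support either. ANOVA may be meant for the pain score, which has its own subgroup analyses. Neither the odds nor the risk scale is privileged, and the larger discrepancy in step 5 needs a treated live birth rate that the article nowhere anticipates.

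**Conclusion.** The point holds as a modest improvement. The design uses strata that the stated primary analysis does not name. Followed literally, the analysis is valid and slightly conservative: under the assumed spreads the PIP-IVF standard error is about 1–5% too large, type I error is about 3.6–4.8%, and the power loss is 0 to 2 points. At the planned PIP-IVF effect the loss is negligible. It would matter a little more if the true effect is smaller than planned, and the sample size section itself acknowledges growing doubt about benefit.

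These figures rest on between-stratum differences that the article does not give, on equal clinic sizes and on exact balance within strata. Incomplete blocks in small clinics would make the balance only approximate. If strata do not predict live birth, nothing is lost either way.

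**What to change.** State that the primary estimate in each trial is a risk ratio adjusted for the randomisation strata: clinic in all three, plus fresh/frozen-thaw transfer in PIP-IVF. Use either Mantel-Haenszel, or modified Poisson regression with robust standard errors. Fix in advance how small clinics are pooled, which matters most in PIP-UE (350 women) and PIP-PCOS (280 women). Report the unadjusted risk ratio as support.

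Optionally, test subgroup interactions for live birth on the risk-ratio scale, so that they match the main effect, and say which outcomes ANOVA is meant for.

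The cost is analysis wording and one pooling rule. No extra data or recruitment is needed, because clinic and transfer type are already recorded at randomisation.
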